### Inclusion criteria

1. Participants must have symptomatic and asymptomatic Diverticular disease confirmed on endoscopy/ *telescope test, barium enema or CT scan*

*(Symptomatic disease is define as lower abdominal pain >1hr on 3 or more days per month for longer than 3 months.)*

1. 18 – 85 years of age.
2. Signed informed consent

### Exclusion criteria

General exclusions

1. Pregnant or lactating women.
2. Severe co-morbidity; e.g. heart failure, respiratory failure, alcoholism or drug dependence,
3. Inability to give informed consent.
4. If the participant has taken part in any other study on campus in the last 3 months they will not be able to take part in this study.
5. Inability to lie supine
6. Inability to stop laxatives for 24hrs and antispasmodics or ondansetron for 8 hours prior to the commencement of the MRI study.
7. Using long-term NSAIDs (non-steroidal anti-inflammatory agents e.g. ibuprofen), antibiotics or immunosuppressant drugs
8. Antibiotics within last 3 months
9. Other gastrointestinal inflammatory problems e.g. ulcerative colitis, Crohn’s or Coeliac disease

MRI exclusions

1. Have a metallic implant e.g.
   1. Cardiac pacemaker or Implanted cardiac defibrillator
   2. Metallic heart valves
   3. Aneurysm clips
   4. Carotid artery vascular clamp
   5. Neurostimulator
   6. Insulin or infusion pump or implanted drug infusion device
   7. Non-removable cochlear, otologic, or ear implant
2. Have shrapnel inside the body
3. Ever had metallic fragments in the eye
4. Claustrophobia

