## SECONDARY OBJECTIVES

Differences between:

1. Adiponectin and leptin serum levels between symptomatic and asymptomatic DD groups
2. The incidence of diarrhoea between participants with a BMI <25Kgm-2 and those >25Kgm-2.
3. Adiponectin and leptin serum levels between DD groups with and without diarrhoea
4. Small and large bowel water and lumen diameter in symptomatic and asymptomatic DD groups
5. Calprotectin levels between symptomatic and asymptomatic DD groups.
6. Microbiological gut profile between symptomatic and asymptomatic DD groups.

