## MRI study day protocol

Participants will be required to make 1 visit to the department. Prior to the visit we will ask participants to complete a 14 day bowel habit diary sheet and provide a stool sample, to bring on the day of their MRI visit.

The participants will visit the ***Brain and Body Centre*** after a overnight fast (fast of 12 hrs food and 6 hr for clear fluids). They will be asked to omit any laxatives for 24hrs and antispasmodics for 12hrs prior to the MRI study day. The participants will be screened and consented for the MRI study. They will have baseline pulse, blood pressure, height and weight, waist and hip circumference measured and recorded and will complete a safety questionnaire to ensure there are no contraindications to MRI (i.e. have metal implants or pacemaker).

Participants will be shown the 1.5T MRI Philips Achieva scanner. They will be positioned supine in the scanner with a parallel imaging body coil wrapped around the abdomen. Several different imaging sequences will used to optimally image the different regions of the gut as follows;

1. SBWC will be assessed with a single shot, fast spin echo sequence. This scan will take approximately 10 minutes.
2. A dual-gradient echo imaging sequence will be used to visualize anatomy. This scan will take approximately 10 minutes.

Including set-up and imaging, the volunteers spend approximately 20 minutes inside the magnet.

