## STUDY REGIMEN

Please see diagram below.

[figure not shown]

Participants who have completed the questionnaires will be invited to attend the MRI scanning session if they;

1. Are confirmed to have a radiological or endoscopic diagnosis of diverticular disease
2. Meet the inclusion or exclusion criteria

It is expected that up to 500 potential participants will be sent the letter of introduction and questionnaires to obtain 105 participants who meet the study criteria.

Participants will attend the MRI scanning session after a overnight fast (fast of 12 hrs food and 6 hr for clear fluids). They will be asked to omit any laxatives for 24hrs and antispasmodics for 12hrs prior to the MRI study day.At all over times of the study, participants can take their normal medication and eat and drink whenever they like. This request is made as they can interfere with the measurement of small and large bowel water content.

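### The exclusion criterion asks for 8 hours off antispasmodics or ondansetron before MRI, but the study-day instructions ask for 12 hours off antispasmodics and omit ondansetron

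*Protocol*

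**What the plan says.** Three places in the protocol deal with stopping medication before the scan.

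- **Exclusion criteria, general item 6** excludes anyone with "Inability to stop laxatives for 24hrs and antispasmodics or ondansetron for 8 hours prior to the commencement of the MRI study".
- **MRI study day protocol** tells participants: "They will be asked to omit any laxatives for 24hrs and antispasmodics for 12hrs prior to the MRI study day".
- **Study Regimen** repeats the 24-hour and 12-hour request, allows usual medication at all other times, and gives the reason: "This request is made as they can interfere with the measurement of small and large bowel water content".

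The outcome concerned is item 4 of the secondary objectives: "Small and large bowel water and lumen diameter in symptomatic and asymptomatic DD groups".

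**The concern.** An eligibility rule and a study-day instruction that serve the same purpose should agree on which drugs are stopped, for how long, and counted from when. Here they disagree on the interval and the drug list, and their wording of the reference time differs.

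What is at stake is the comparability of the bowel-water measurements. The protocol itself treats these medicines as a possible source of interference. If screening staff work to one rule and the visit instruction follows another, participants may be scanned after different drug-free periods while all of them satisfy some part of the protocol. The symptomatic groups are defined by recurrent lower abdominal pain, so antispasmodic use may well be more common there. That is an assumption, because the protocol gives no usage figures. If it is right, a drug effect could fall unevenly across the symptomatic versus asymptomatic comparison, and recruiting more participants would not remove it.

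**Working it through.** There is no power, sample size or error-rate figure to reproduce. The check is a comparison of the three texts.

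| Element | Exclusion criteria, item 6 | MRI study day protocol | Study Regimen |
| --- | --- | --- | --- |
| Laxatives | 24 h | 24 h | 24 h |
| Antispasmodics | 8 h | 12 h | 12 h |
| Ondansetron | 8 h | not mentioned | not mentioned |
| Counted back from | start of the MRI study | MRI study day | MRI study day |

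**Interval.** 12 h − 8 h = 4 h. Let T be the longest time a person can go without an antispasmodic.

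- T below 8 h: excluded by item 6.
- T of at least 8 h but below 12 h: not excluded, but unable to meet the 12-hour request.
- T of 12 h or more: not excluded and able to comply.

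The middle band is the group the contradiction creates. The protocol does not say how many people fall in it.

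**Drug list.** Item 6 makes ability to stop ondansetron a condition of entry. The two instruction sections name only laxatives and antispasmodics. A participant taking ondansetron who follows those sections exactly has no instruction to stop it.

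**Reference time.** If the study day is read as the calendar day and the scan starts t hours after midnight, the instruction amounts to 12 + t hours before the scan, and the gap between the two rules becomes (12 + t) − 8 = 4 + t hours. If both phrases mean the start of the visit, the gap is 4 hours. The protocol does not say which is meant.

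**Effect on the bowel-water comparison.** In simple form, the bias in the symptomatic minus asymptomatic difference is (p_S − p_A) × d. Here p_S and p_A are the proportions in each group scanned with residual drug because of the inconsistency, and d is the mean effect of that residual drug on bowel water. The protocol gives none of the three, and no standard deviation for bowel water. The expression shows only what a differential effect requires: a non-zero d and unequal proportions.

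**Outcomes affected.** Study Regimen links the restriction to bowel water only. The primary objective compares visceral with subcutaneous fat, and the sample size of 35 per group rests on visceral fat. Neither depends on the drug-free interval.

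**The case against.** The best defence is that the two rules do different jobs: item 6 sets a minimum for entry, and the instructions set what everyone is asked to do. On that view every participant is asked for 12 hours off antispasmodics, and the inconsistency matters only for the 8-to-12-hour band. Ordinary non-compliance would occur under any single figure. The narrowing is fair, and the exposed antispasmodic users may be few. But the protocol nowhere states a minimum and a target, and this reading does not explain why ondansetron is missing from the instructions.

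The difference in reference time may be no more than loose wording for the same single visit. That is plausible, so it is a point to tidy and not a separate source of error.

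A reader might infer that the protocol regards an interval of 8 to 12 hours as disturbing the measurement. It does not say so. Study Regimen says only that interference is possible, ties it to no interval, and is loose about whether the remark covers the drugs alone or also the fasting. A reader might also want to express the bias in standard deviation units. Any such figure would rest on invented inputs, since usage by group, residual effect and variability are all absent.

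Finally, dose-time recording and sensitivity analyses may properly sit in study forms or an analysis plan, which are not at hand. Their absence is not part of this point. The participant information sheet is also not shown and could mention ondansetron, but that would not make the protocol sections agree.

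**Conclusion.** The contradiction is real. The antispasmodic interval differs by 4 hours between the eligibility rule and the two instruction sections, and ondansetron appears only in the eligibility rule. Followed as written, the protocol admits people who cannot meet its own instruction and does not tell ondansetron users to stop.

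The consequence is limited to bowel water under secondary objective 4. It could add variation there, and could do so unevenly if users are concentrated in the symptomatic groups, which is an assumption. Neither the size nor the direction of any effect can be derived from the protocol. The primary fat comparison and the sample size stand. Which interval is appropriate is a clinical question and is not judged here.

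**What to change.** Amend Exclusion criteria item 6, MRI study day protocol and Study Regimen so that all three give one interval, one reference time and one drug list, with an explicit decision on whether ondansetron belongs in the instructions. The investigators must choose the content. If a minimum for entry and a longer request are both intended, the protocol should say so.

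Optionally, record the time of the last dose of each listed drug at the visit, so that scans outside the reconciled window can be identified when bowel water is analysed.

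The cost is a minor amendment, plus one line on the study-day form if dose times are recorded. Sample size, primary analysis and visit schedule do not change.

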## Biological samples

### Stool samples

Participants will be asked to freeze their stool samples in the domestic freezer prior to bringing it to the B&B centre. Pots, gloves, bags and detailed instructions will be provided to the participants to prevent contamination of food by faeculent material. Samples will be brought to the B&B centre by the participant and frozen at -20oC so that the sample time of >-20oC is kept to a minimum time of 1.5hrs. All samples will be anonymised and stored at -20oC in the Nottingham Digestive Disease Centre freezers. Samples will be analysed for calprotectin and genetic techniques (e.g. quantitative PCR or microarray) to identify diversity of gastrointestinal microflora between groups.

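### As-needed NSAID use before the stool sample is neither excluded nor described as recorded, so it could confound the calprotectin comparison between symptomatic and asymptomatic groups

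*Protocol*

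**What the plan says.** Item 7 of the general exclusions in the protocol reads "Using long-term NSAIDs (non-steroidal anti-inflammatory agents e.g. ibuprofen), antibiotics or immunosuppressant drugs". Item 8 adds a separate look-back for one of those drug classes: "Antibiotics within last 3 months". NSAIDs have no look-back.

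The Study Regimen section names the drugs to be withheld before the scan: "They will be asked to omit any laxatives for 24hrs and antispasmodics for 12hrs prior to the MRI study day". Its reason is "This request is made as they can interfere with the measurement of small and large bowel water content". Apart from that, "At all over times of the study, participants can take their normal medication and eat and drink whenever they like".

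The stool sample is produced at home before the visit: "Participants will be asked to freeze their stool samples in the domestic freezer prior to bringing it to the B&B centre". The day of collection within the diary period is not fixed.

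The Inclusion criteria define symptomatic disease as "lower abdominal pain >1hr on 3 or more days per month for longer than 3 months". Item 5 of the Secondary Objectives compares "Calprotectin levels between symptomatic and asymptomatic DD groups". The Participant groups section matches on age and sex, and the Statistics section specifies two-sided unpaired t or Mann–Whitney tests without covariates.

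**The concern.** The compared groups are separated by recurrent pain, and the example drug in item 7, ibuprofen, is a painkiller. It is therefore plausible that as-needed NSAID use is more common in the symptomatic groups. Matching on age and sex does not remove an imbalance that arises from the variable defining the groups, and the planned tests do not adjust for it.

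If short-term NSAID use raises calprotectin, the distortion would point the same way as the inflammatory mechanism that the Background proposes for symptomatic disease. A positive result on endpoint 5 could then not be separated from analgesic use. No later analysis plan can repair this unless the exposure was recorded at the time.

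**Working it through.** **What the plan gives.** It has no figure for calprotectin or for NSAID use. Its only sample-size figure is 35 per group for a 30% difference in visceral fat at 90% power. No SD is stated, so the figure can only be back-solved: SD = 0.30 / [(1.960 + 1.282) × √(2/35)] = 38.7% of the mean, two-sided. That neither supports nor weakens this point.

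**Ratio of means with no disease effect.** Let a and b be the proportions using an NSAID before the sample in symptomatic and asymptomatic participants, and k the fold rise in calprotectin in users. All three are assumptions.

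Ratio = (1 − a + ak) / (1 − b + bk)

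- a = 15%, b = 5%, k = 1.5: 1.075 / 1.025 = 1.05
- a = 25%, b = 5%, k = 2: 1.25 / 1.05 = 1.19
- a = 40%, b = 10%, k = 3: 1.80 / 1.20 = 1.50

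**Effect on the planned test.** Log-calprotectin was simulated with no true group difference and an assumed SD of 1.0 on the log scale, with 5,000 runs per scenario and a Mann–Whitney test at a nominal two-sided 5%. The group sizes were 70 v 35, which pools the two symptomatic groups (the protocol does not say whether they are pooled). The spurious geometric mean ratio is k^(a − b).

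| NSAID use, symptomatic v asymptomatic | 1.5-fold rise | 2-fold rise | 3-fold rise |
|---|---|---|---|
| 20% v 10% | 5.7% | 6.0% | 7.5% |
| 30% v 10% | 6.6% | 9.2% | 14.3% |
| 40% v 10% | 9.0% | 14.6% | 30.2% |
| 50% v 10% | 11.4% | 23.9% | 48.2% |

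Across the table the geometric mean ratio runs from 1.5^0.1 = 1.04 to 3^0.4 = 1.55. With 35 v 35 the false-positive rates run from 5.2% to 36.5%. With no use, or with 10% in both groups, the rates were 3.9% to 5.8%, so the 5.7% in the first cell cannot be told apart from the nominal level. The excess comes from the imbalance, and equal use removes it.

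**The case against.** The strongest case against has five parts.

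- **The causal step is not in the document.** Nothing in the protocol says that NSAIDs, least of all short courses, raise calprotectin, and item 7 gives no reason for its exclusion. The imbalance between groups is also assumed. This stands: the point is one of possible confounding, not demonstrated bias.
- **Long-term is undefined.** Someone who takes an NSAID for every pain episode over more than three months might be judged a long-term user and excluded, which would leave only sporadic use. This may shrink the gap but does not close it, because nothing addresses short or recent use.
- **The antibiotic look-back may have its own purpose.** A reader might infer that the authors closed a gap for antibiotics and overlooked the same gap for NSAIDs. The protocol does not support that: the three-month rule may serve the microbiological profile (secondary endpoint 6). The missing NSAID rule is not a contradiction.
- **The analysis plan and the diary form are not shown.** Either could deal with medication. However, the protocol describes the diary as covering bowel habit and pain and mentions no record of NSAID use. An adjustment in an analysis plan would depend on such a record.
- **Restriction can itself bias.** One might want to make participants without NSAID use the main comparison. On the same reasoning that makes NSAID use a concern, this would drop symptomatic participants with more pain, and with them possibly true signal. This stands, and it is why that comparison should be supportive only.

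**Conclusion.** The point holds in a limited form. As written, the protocol excludes only long-term NSAID users, permits normal medication while the sample is produced, and compares pain-defined groups by unadjusted tests. As-needed NSAID use could therefore confound endpoint 5.

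The size is unknown from the document. It rests on assumed usage rates, an assumed fold rise and, for the error rates, an assumed SD. A small imbalance barely moves the result (ratio 1.05; false-positive rate 5.7% to 7.5% at 20% v 10% use). A large imbalance with a large rise matters (ratio 1.50; false-positive rate 30.2% at 40% v 10% use and a 3-fold rise).

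A reader might infer that any calprotectin difference in this study would be false, or that the eligibility rule is wrong. The document supports neither. The effect is confined to one of six secondary endpoints in a pilot study, and the Transport and Storage section leaves open whether stool will be analysed for calprotectin, for organisms or for both. The primary visceral fat endpoint is unaffected.

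**What to change.** Before data collection:

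1. Record any NSAID use in the 14 days up to the stool sample. Add one column to the existing diary and one question at sample hand-over, and note the sample date. The question is needed because a sample produced early has little diary before it, and the Compliance section accepts 10 completed days.
2. Report NSAID use by group.
3. Keep the all-participant calprotectin comparison as the main one. Prespecify a supportive comparison in participants with no recorded NSAID use, or one adjusted for use.
4. State that a calprotectin difference will be attributed to symptomatic DD only if the two comparisons agree.

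The cost is one extra data item and a smaller supportive comparison that may under-represent participants with more pain. If everyone provides a sample and the symptomatic groups are pooled, use of 25% v 5% would leave about 70 × 0.75 = 52.5 and 35 × 0.95 = 33.25 participants; use of 40% v 10% would leave 70 × 0.60 = 42 and 35 × 0.90 = 31.5. No change to eligibility or treatment is proposed.

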### Expected duration of participant participation

Study participants will be participating in the study for 14 days

### Participant Withdrawal

Participants may be withdrawn from the study either at their own request or at the discretion of the Investigator. It will also be explained that they can withdraw at any time but attempts will be made to avoid this occurrence. The participants will be made aware that this will not affect their future care. In the event of their withdrawal it will be explained that their data collected so far cannot be erased and we will seek consent to use the data in the final analyses where appropriate. Remaining tissue samples will be destroyed if the participant so wishes.

### Informed consent

All participants will provide written informed consent. The Consent Form will be signed and dated by the participant before they enter the study. The Investigator will explain the details of the study and provide a Participant Information Sheet, ensuring that the participant has sufficient time to consider participating or not. The Investigator will answer any questions that the participant has concerning study participation.

Informed consent will be collected from each participant before they undergo any interventions (including physical examination and history taking) related to the study. One copy of this will be kept by the participant, one will be kept by the Investigator, and a third will be retained in the patient’s hospital records.

Should there be any subsequent amendment to the final protocol, which might affect a participant’s participation in the study, continuing consent will be obtained using an amended Consent Form which will be signed by the participant.

If needed, the usual hospital interpreter and translator services will be available to assist with discussion of the trial, the participant information sheets, and consent forms, but the consent forms and information sheets will not be available printed in other languages. It will be explained to the potential participant that that entry into the study is entirely voluntary and that their treatment and care will not be affected by their decision. It will also be explained that they can withdraw at any time but attempts will be made to avoid this occurrence. In the event of their withdrawal it will be explained that their data collected so far cannot be erased and we will seek consent to use the data in the final analyses where appropriate.

## STUDY REGIMEN

Please see diagram below.

[figure not shown]

Participants who have completed the questionnaires will be invited to attend the MRI scanning session if they;

1. Are confirmed to have a radiological or endoscopic diagnosis of diverticular disease
2. Meet the inclusion or exclusion criteria

It is expected that up to 500 potential participants will be sent the letter of introduction and questionnaires to obtain 105 participants who meet the study criteria.

Participants will attend the MRI scanning session after a overnight fast (fast of 12 hrs food and 6 hr for clear fluids). They will be asked to omit any laxatives for 24hrs and antispasmodics for 12hrs prior to the MRI study day.At all over times of the study, participants can take their normal medication and eat and drink whenever they like. This request is made as they can interfere with the measurement of small and large bowel water content.

### Compliance

The questionnaires and diary sheets will be assessed at the MRI scanning visit. The participant will be accepted as compliant if they have completed the bowel symptom questionnaire and at least 10 days or more of the diary sheet. Failure to provide a stool sample will not result is exclusion from taking part further in the MRI scanning or blood sampling aspects of the study.

